### Inclusion criteria

1. Patients aged 18 to 65 years

2. Patients will be recruited both from inpatients and outpatients.

3. Diagnostic and Statistical Manual-IV (DSM-IV TR) diagnosis of schizophrenia, schizoaffective disorder, psychosis not otherwise specified or schizophreniform disorder

4. Competent and willing to give informed consent

5. Stable on medication four weeks prior to baseline

6. No planned medication change

7. Able to take oral medication and likely to complete the required evaluations

8. Female participants of child bearing age must be willing to use adequate contraceptives for the duration of the study and be willing to have a pregnancy test pre-treatment and at 10 weekly intervals while on study medication,

9. Not planning to relocate in the next 12 months

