### Interval of assessments

There will be a screening, a randomization and seven follow-up visits. Full clinical and neurocognitive assessments will be carried out at baseline (randomization), 14 weeks and at 26 weeks, while PANSS, pill count and side effects checklist will be carried out at every visit. The clinical interview and ratings will take approximately 50 minutes. The neuropsychological assessments will take about 60 to 80 minutes. The patients will primarily be seen at their treating team’s base. In special circumstances, if requested by the treating team or patient, the RAs can visit at home (Table 3).

**Table 3 T3:** Schedule of assessments

**Assessment**	**Who**			**When**								
	**Pt.**	**RA**	**RMO**	**Scr.**	**Rand.**	**W 2**	**W 6**	**W10**	**W14**	**W18**	**W22**	**W26**
**Case note review**			x									x
**SCID**		x		x								
**Drug treatment history**		x		x	x	x	x	x	x	x	x	x
**Medical history**			x	x								
**Physical exam**		x		x								x
**Body weight and BMI**		x			x				x			x
**BP and HR**		x		x	x	x	x	x	x	x	x	x
**Lab screen**			x	x					x			x
**Pregnancy screen (urine)**		x			x			x	x			x
**Inclusion criteria**		x		x								
**Exclusion criteria**		x		x								
**Withdrawal criteria**		x			x	x	x	x	x	x	x	
**Consent**	x	x		x	x							
**PANNS**		x			x	x	x	x	x	x	x	x
**CGI**		x			x	x	x	x	x	x	x	x
**GAF**		x			x				x			x
**QOL**		x			x				x			x
**Social function Scale**		x			x				x			x
**Cognitive assessments**		x			x				x			x
**Antipsychotic side effects**		x			x	x	x	x	x	x	x	x
**Side effects simvastatin/ondansetron**	x	x			x	x	x	x	x	x	x	x
**Compliance monitoring**		x				x	x	x	x	x	x	x

(Pt. Patient; RA, Research Assisstant; RMO, Reseident Medical Officer; W2, Week2; W6, Week 6; W10, Week10; W14, Week14; W18, Week18; W22, Week22; W26, Week26).

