#### Randomization visit

The baseline clinical and neuropsychological measures will be completed and the patient will be randomized to one of the four study arms, allocated a unique identification number and will commence study drug treatment.

The patient will be given a study information card explaining that they are in a clinical study and are taking simvastatin or ondansetron, the telephone numbers of the senior research clinicians, the clinical trial office and the name of the local PIs.

In accordance with (International Conference for Harmonisation) Good Clinical Practice ((ICH)GCP) copies of all the above will be placed in the patient’s medical notes along with contact names and telephone numbers.

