##### Follow-up visits

The first follow-up visit will be after two weeks of the randomization to check for safety and tolerability of the treatment initiated. There will be visits at week 6, 10, 14, 18 and 22. On all these visits the patients will collect their trial treatment from their treatment centers. The study drugs at the two sites will be dispensed from the local pharmacy departments. The research assistants will collect and deliver these to the patient at a previously agreed upon location. This will give the opportunity for the research team to closely monitor the patient’s physical and mental health, side effects and compliance (by pill count).

Female patients with childbearing capacity taking part in the clinical trial will have a pregnancy test on a regular basis. If they should become pregnant during the course of the study, they will be withdrawn from the study.

During the course of the study the patient’s individual consultant and mental health care team will be responsible for their overall care. If any concerns do occur with regard to the research study, the research team can be contacted to discuss these concerns 24 h a day 7 days per week. The patient will have their study card with the telephone number of the research clinicians and clinical trial office if they have any concerns or questions.

One of the co-investigators and/or the study doctor will be available 24 h per day 7 days per week and will be contacted by the patient or carers or the research clinicians should this be necessary.

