#### 26 week, final visit

At this visit all clinical, neuropsychological, physical and hematological assessments will be completed. Trial medication will cease.

At all visits the patient’s cumulative clinical drug treatment will be updated from the case notes.

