#### Patient withdrawal

Patients may be withdrawn from the treatment study for the following reasons:

1. At their own request.

2. At the discretion of the investigator.

3. If any patients suffers a serious adverse event, or moderate to severe adverse drug reaction.

4. Any patients meet the criteria for insufficient compliance. This is defined as either taking less than 75% of antipsychotic or trial medication between assessment points at baseline, 14 and 26 weeks; or missing trial medications or antipsychotic altogether for seven days or more at any period.

5. If a patient becomes pregnant.

They may withdraw from the study entirely (that is, follow-up) at their own request or at the investigator’s discretion.

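### Table 3 leaves 12 weeks on study drug (W14 to W26) without a pregnancy test, against the 10-weekly interval in inclusion criterion 8

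*Protocol article*

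**What the plan says.** Three places in the protocol article bear on how often pregnancy is tested.

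- **Inclusion criteria, item 8** gives the only numeric rule: women must "be willing to have a pregnancy test pre-treatment and at 10 weekly intervals while on study medication".
- **Table 3 (Interval of assessments)** marks the urine test under Rand., W10, W14 and W26. There is no mark under W2, W6, W18 or W22.
- **Follow-up visits** says "Female patients with childbearing capacity taking part in the clinical trial will have a pregnancy test on a regular basis", without giving an interval.

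The period on drug is fixed by two further sections. At the Randomization visit the patient "will commence study drug treatment", and under the 26 week, final visit, "Trial medication will cease". Under Patient withdrawal, item 5 lists "If a patient becomes pregnant" as a reason to stop study treatment.

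**The concern.** The article prints both a testing rule and a testing schedule, and the two disagree. This is a conflict between two stated items, not a detail left to a fuller document.

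What is at stake is participant safety. Pregnancy excludes a woman at entry and is a ground for withdrawal during treatment. Scheduled testing exists to find a pregnancy that nobody has yet recognised. The W26 test coincides with the end of medication, so W14 is the last scheduled test that could take a woman off study drug. A site that follows Table 3 exactly will exceed the criterion 8 interval for every woman of child-bearing age who stays on drug to W26.

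**Working it through.** **Inputs**

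- Stated interval: 10 weeks, plus one test before treatment (Inclusion criteria, item 8).
- Scheduled tests: weeks 0, 10, 14 and 26 (Table 3, pregnancy row).
- Time on drug: week 0 (Randomization visit) to week 26 (final visit).
- Visits between those two: W2, W6, W10, W14, W18 and W22 (Table 3).

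**Is the row read correctly?** The row has 13 cells, matching the 13 header columns. As a cross-check within the same table, the cognitive row falls at Rand., W14 and W26, which agrees with the text above the table. A shifted column is therefore not the explanation.

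**Intervals as scheduled**

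| From | To | Weeks | At most 10? |
|---|---|---|---|
| Rand. | W10 | 10 − 0 = 10 | yes |
| W10 | W14 | 14 − 10 = 4 | yes |
| W14 | W26 | 26 − 14 = 12 | no, 12 − 10 = 2 over |

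After the W14 test the next was due by week 14 + 10 = 24. W18 and W22 both fall before then. The untested stretch is 12 of 26 treatment weeks (12/26 = 46%).

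**Can the visit grid meet the rule?** Strict 10-weekly testing would fall at W10 and W20, and there is no W20 visit. An interval of at most 10 weeks is achievable, with tests kept at weeks 0 and 26:

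- *Two interim tests, as now.* There are 15 ways to choose two of the six interim visits. The first must be at W10 or earlier and the second at W16 or later, which means W18 or W22. Among these, only W10 with W18 also keeps the middle interval within 10 weeks: 10, 8, 8.
- *W10 and W14 kept, one test added.* W18 gives 10, 4, 4, 8 and W22 gives 10, 4, 8, 4; both meet the limit. W2 (2, 8, 4, 12) and W6 (6, 4, 4, 12) do not.
- *W14 moved to W22.* This gives 10, 12, 4, which fails in the same way as the present schedule.

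**The case against.** The mismatch itself is not in doubt; the argument on the other side is about its weight.

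- **Table 3 tests more often than a strict reading of criterion 8:** three on-drug tests (W10, W14, W26) against two (W10, W20). Suppose conception is equally likely at any time over 26 weeks and is always found at the next test. The mean wait is then the sum of squared intervals divided by 2 × 26 = 52. Table 3 gives (100 + 16 + 144)/52 = 5.0 weeks. Tests at W10, W20 and W26 give (100 + 100 + 36)/52 = 4.5 weeks, and W10, W18 and W26 give (100 + 64 + 64)/52 = 4.4 weeks. The average difference is about half a week. This stands, and it is why the point is minor. It does not remove the conflict over the longest interval.
- **Criterion 8 is an eligibility condition about willingness, and its figure cannot be applied literally on this visit grid.** Reading it as a maximum is an interpretation, though a reasonable one. On either reading, 12 weeks is not 10.
- **Other safeguards exist.** Contraception is required, and the "Withdrawal criteria" row of Table 3 is marked at W18 and W22. This also stands, but that review acts only on a pregnancy already recognised.
- **The row may not list every test.** The Screening visit section mentions pregnancy testing where appropriate, and Table 3 has no mark under Scr. That is a second discrepancy in the same row. It does not supply a test at W18 or W22.

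**Conclusion.** The schedule is wrong as written. One of three on-drug intervals is 12 weeks against a stated 10, an excess of 2 weeks, and no other section resolves the difference. The conclusion assumes that criterion 8 is meant to govern on-drug testing and that Table 3 is the schedule sites follow. The consequence is limited to late detection of an unrecognised pregnancy after W14. Sample size, power and the analysis of the primary outcome are unaffected. It should be corrected because it concerns participant safety and the correction is cheap.

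**What to change.** Change the pregnancy row of Table 3 in one of two ways:

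1. Keep W14 and add one urine test at W18 or W22. The longest interval becomes 10 weeks, and the W14 test stays with the full assessment and laboratory screen. The cost is one extra urine test per woman of child-bearing age. It falls at an existing visit and is done by the research assistant, who is already marked for this test and already carries out other assessments at W18 and W22.
2. Move the W14 test to W18. The longest interval is again 10 weeks with no extra test, but the urine test is separated from the W14 assessments and the present 4-week interval after W10 becomes 8 weeks.

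In either case, reword criterion 8 to require testing before treatment and then at intervals of no more than 10 weeks on study medication. In the same edit, bring the screening column of the row into line with the Screening visit section. The Trial status section describes the study as recruiting, so this changes the schedule and an inclusion criterion mid-trial. It has no effect on sample size or analysis.

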### Exclusion criteria

1. Relevant International Statistical Classification of Diseases and Related Health Problems (ICD)-10 organic brain disease or neurological diagnoses (including ECG conduction abnormalities, neurological disorder or an active seizure)

2. Subjects who will meet the criteria for a DSM-IV TR diagnosis of alcohol or substance abuse (other than for nicotine) within the last month or the criteria for DSM-IV TR alcohol or substance dependence (other than for nicotine) within the last six months

3. Any change of psychotropic medications within the previous four weeks

4. Pregnant or lactating women and those of reproductive age without adequate contraception

### Interval of assessments

There will be a screening, a randomization and seven follow-up visits. Full clinical and neurocognitive assessments will be carried out at baseline (randomization), 14 weeks and at 26 weeks, while PANSS, pill count and side effects checklist will be carried out at every visit. The clinical interview and ratings will take approximately 50 minutes. The neuropsychological assessments will take about 60 to 80 minutes. The patients will primarily be seen at their treating team’s base. In special circumstances, if requested by the treating team or patient, the RAs can visit at home (Table 3).

**Table 3 T3:** Schedule of assessments

**Assessment**	**Who**			**When**								
	**Pt.**	**RA**	**RMO**	**Scr.**	**Rand.**	**W 2**	**W 6**	**W10**	**W14**	**W18**	**W22**	**W26**
**Case note review**			x									x
**SCID**		x		x								
**Drug treatment history**		x		x	x	x	x	x	x	x	x	x
**Medical history**			x	x								
**Physical exam**		x		x								x
**Body weight and BMI**		x			x				x			x
**BP and HR**		x		x	x	x	x	x	x	x	x	x
**Lab screen**			x	x					x			x
**Pregnancy screen (urine)**		x			x			x	x			x
**Inclusion criteria**		x		x								
**Exclusion criteria**		x		x								
**Withdrawal criteria**		x			x	x	x	x	x	x	x	
**Consent**	x	x		x	x							
**PANNS**		x			x	x	x	x	x	x	x	x
**CGI**		x			x	x	x	x	x	x	x	x
**GAF**		x			x				x			x
**QOL**		x			x				x			x
**Social function Scale**		x			x				x			x
**Cognitive assessments**		x			x				x			x
**Antipsychotic side effects**		x			x	x	x	x	x	x	x	x
**Side effects simvastatin/ondansetron**	x	x			x	x	x	x	x	x	x	x
**Compliance monitoring**		x				x	x	x	x	x	x	x

(Pt. Patient; RA, Research Assisstant; RMO, Reseident Medical Officer; W2, Week2; W6, Week 6; W10, Week10; W14, Week14; W18, Week18; W22, Week22; W26, Week26).

### RA training and interrater reliability

Research assistants in Karachi were trained in Structured Clinical Interview for DSM-IV (SCID), clinical and neuropsychological assessments at the University of Manchester for a previous SMRI funded study. Interrater reliability sessions will be conducted by local PIs, using training videos.

### Treatments

#### Treatment as usual

The patients can either be on first or second generation antipsychotic medications, as deemed suitable by the responsible psychiatrist. From our experience with previous study across the two centers in 144 patients, the distribution was approximately 50:50 between the two generations of antipsychotics.

#### Study drug dosage

Simvastatin will be started at 20 mg OD, this will be increased to 40 mg after four weeks. The dose range for hypercholesterolemia is from 10 mg to 80 mg once daily. We are not concerned with this drug’s performance in this indication; therefore, we consider 40 mg taken as one daily dose appropriate for the purposes of this research study. Statins have been used commonly with psychotropics for many years.

Ondansetron will be administered in an 8 mg dose. British National Formulary (BNF) specifies an 8 mg once daily dose. Studies by Akhondzadeh *et al.*[12] and Levkovitz *et al.*[13] have used 8 mg of ondansetron added to TAU with good tolerability in patients suffering from schizophrenia. Ondansetron is well tolerated, has no significant drug interaction reported, is broken down by cytochrome P450 and has little effect on metabolism of other drugs. It is often combined with psychotropic medication. There is no known indication of unexpected clinically significant interactions.

### Outcome variables

#### Primary clinical outcome variable

Negative symptom severity is defined by the negative syndrome subscale score on the Positive and Negative Syndrome Scale, which is the gold standard for comprehensively rating symptoms of schizophrenia [16].

#### Secondary clinical outcome variables

1. Full PANSS and positive syndrome subscale score [16]

2. Clinical Global Impression

3. Functional outcome:

•Global Assessment of Function (GAF) from DSM-IV [17]

•Social Functioning Scale (SFS) self-rating in seven domains [18]

•Quality of Life Scale (QLS) for treatment effects related to deficit or negative symptoms [19]

### Secondary cognitive outcome measures

We will use pencil and paper tests and the Cambridge Neuropsychological Test Automated Battery (CANTAB); measuring all seven domains recommended by MATRICS (NIMH initiative). These domains include speed processing, attention/vigilance, working memory (nonverbal and verbal), verbal learning, visual learning, reasoning and problem solving, and social cognitions. We will use the following tests:

1. IQ: using WAIS Block design

2. Stroop Task, for divided attention and processing speed

3. Coughlan Learning Task (Verbal and Visual)

4. Verbal Fluency (words and categories)

5. CANTAB

•Intra-Extra Dimensional Set Shifting (IED), which tests rule acquisition and attentional set shifting

•Spatial Working Memory (SWM), which tests working memory and strategic planning.

•Paired Associates Learning (PAL), which assesses episodic memory and learning

#### Side effects

Self-reported antipsychotic side-effects: Antipsychotic Non-neurological Side-Effects Rating Scale [20].

### Safety assessments

#### Medical history

The primary purpose of screening is to check for inclusion and exclusion criteria. The RAs will arrange for a doctor to complete checklists for medical history, review of systems, a physical exam and arrange a blood draw for hematology and differential white cell count, and for clinical chemistry to confirm normal renal and liver function. These assessments will be repeated after six months in the trial or at the time of withdrawal from the study.

#### Physical assessments

Physical assessments will include ECG, Blood pressure, pulse, height, waist, weight and body mass index (BMI).

#### Blood investigations

Blood investigations will include full blood count, erythrocyte sedimentation rate, liver function tests, lipid profile, urea, electrolytes and C-reactive protein.

#### Adverse events

An adverse event (AE) is the development of an undesirable medical condition or the deterioration of a pre-existing medical condition following or during exposure to a pharmaceutical product, whether or not considered causally related to the product. An undesirable medical condition can be symptoms (for example, nausea, chest pain), signs (for example, tachycardia, enlarged liver) or the abnormal results of an investigation (for example, laboratory findings, electrocardiogram). In clinical studies, an AE can include an undesirable medical condition occurring at any time, including run-in or washout periods, even if no study treatment has been administered.

The open question “Have you had any health problems since you were last asked?” will be used to evoke spontaneous reports of side effects. A self-completed checklist of adverse events derived from those specified in the data sheets for ondansetron and simvastatin will also be administered. Spontaneous and self-rated side-effects will be evaluated for intensity and seriousness.

### Study procedures

#### Recruitment

The psychiatry consultants responsible for patient care will be approached and asked if they will allow their patients to take part in this research study.

In the first instance, the research clinician will approach the clinical teams to inform them about the research study, especially with regard to inclusion and exclusion criteria. The research clinician will establish good working relationships with the individual clinical teams. They will be in regular contact either by phone or by visits to determine, in collaboration with the clinical team, if patients are suitable to take part in the research study. If patients meet the entry criteria, are clinically stable, and the consultant psychiatrist and the clinical team agree the patient could be a possible participant, the consultant will introduce the study to the patient. With the patient’s agreement, the research clinician will visit the patient to explain the research study verbally and provide them with the patient information sheet. After the patient has had time to read and understand the patient information sheet (at least 24 h) and is willing to take part, a meeting (visit one) will be set up with the patient in order to obtain consent for the research and also consent for the research team to have access to their medical notes.

#### Screening visit

Confirmation of patient suitability will be carried out at this point. This will take the form of checking the Inclusion/Exclusion criteria, confirmation of diagnosis, confirmation of consent and pregnancy testing, if appropriate. The RAs will arrange for a doctor to complete checklists for medical history, physical examination and hematological investigations.

#### Randomization visit

The baseline clinical and neuropsychological measures will be completed and the patient will be randomized to one of the four study arms, allocated a unique identification number and will commence study drug treatment.

The patient will be given a study information card explaining that they are in a clinical study and are taking simvastatin or ondansetron, the telephone numbers of the senior research clinicians, the clinical trial office and the name of the local PIs.

In accordance with (International Conference for Harmonisation) Good Clinical Practice ((ICH)GCP) copies of all the above will be placed in the patient’s medical notes along with contact names and telephone numbers.

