## Methods/design

### Overview

This is a two center, six-month, double-blind placebo-controlled, factorial design study of ondansetron and/or simvastatin added to treatment as usual for patients suffering from schizophrenia, schizoaffective disorder, psychosis not otherwise specified or schizophreniform disorder. This will be a 2 × 2 factorial design, with 54 patients in each cell, giving a total of 216 patients over three years (Table 1).

**Table 1 T1:** 2 × 2 Factorial design

	**Placebo**	**Simvastatin**	**Total**
Placebo	54	54	108
Ondansetron	54	54	108
Total	108	108	

The advantage of a factorial design is the effective sample size for each drug is 108 for each treatment factor. However, in addition it allows a test of scientifically and clinically interesting possibility that the two drugs have additive or even multiplicative benefits. A possible minor disadvantage is that all participants take two types of pills.

The study will be conducted in Karachi, Pakistan and San Paulo, Brazil. The patients will be recruited both from inpatient and outpatient settings. The patients will be identified and first approached by the treating psychiatrists and the multi-disciplinary teams (MDT). The patients will continue to take treatment as usual during the trial. While the study assessments will be done by the research assistants (RAs), the responsible psychiatrist will remain in charge of the overall treatment. Any changes to dose or types of medications will be recorded on monthly reviews.

After consenting to take part in the study, the clinical symptoms, cognitive, neurological and general level of function of the participants will be assessed. When these measures are completed, the patient will be randomized to one of the four treatment arms. During the course of the study the patient will also have additional support by doctors and RA from the research team and continued support from their mental health care team. If necessary, members of the research team will be available 24 hours a day, 7 days a week.

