### Allocation

In this study patients will be allocated to treatment group according to a randomized permuted blocks algorithm, after stratification by center. Allocation will be determined in Manchester by pseudo-random number generation by the trial statistician. The results will be conveyed to the trial pharmacist so that medication can be given to participants without anyone else on the team being aware of the allocation (that is, double blind).

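### The study card, as described, tells every patient that they take simvastatin or ondansetron, which does not fit a placebo-controlled 2 × 2 design

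*Protocol article*

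**What the plan says.** The design is set out in the Overview of the protocol article, which describes a "double-blind placebo-controlled, factorial design study of ondansetron and/or simvastatin added to treatment as usual". The Overview gives its size as follows: "This will be a 2 × 2 factorial design, with 54 patients in each cell, giving a total of 216 patients over three years". Table 1 shows the four cells: placebo with placebo, simvastatin alone, ondansetron alone, and both drugs. The Overview also remarks: "A possible minor disadvantage is that all participants take two types of pills".

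Under Allocation, the trial statistician generates the allocation and the pharmacist receives it. The stated purpose is as follows: "medication can be given to participants without anyone else on the team being aware of the allocation (that is, double blind").

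Under Randomization visit, "the patient will be randomized to one of the four study arms, allocated a unique identification number and will commence study drug treatment". The next paragraph reads: "The patient will be given a study information card explaining that they are in a clinical study and are taking simvastatin or ondansetron". The same sentence adds telephone numbers for the senior research clinicians and the trial office, and the names of the local principal investigators. Citing good clinical practice, the section then says that "copies of all the above will be placed in the patient’s medical notes along with contact names and telephone numbers".

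The article gives no other account of what the card says, and it describes no version of the card that differs by arm.

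**The concern.** The card is described as stating a fact about the holder's treatment. It is not worded as a possibility, and it leaves out placebo and the combination. Elsewhere the article writes 'and/or' when it means to include the combination, so the plain 'or' here is a departure from its own usage.

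Two things are at stake. The first is what participants are told: patients in the placebo-only cell would carry a document saying that they take an active drug. The second is what a clinician outside the trial would learn. The responsible psychiatrist stays in charge of overall treatment, patients are told to use the card if they have concerns, and a copy sits in the notes. Someone who relied on the card alone would not learn that the holder may be on two study drugs or on none.

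**Working it through.** **Inputs**

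- Cell size 54, four cells, total 216 (Overview and Table 1).
- Treatment in each cell (Table 1): A, placebo with placebo; B, simvastatin; C, ondansetron; D, both. The letters are those of Table 2.
- Card statement: the holder is taking simvastatin or ondansetron (Randomization visit).
- Recipients: patients in any of the four arms, with no variant by arm described (Randomization visit).

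**Step 1. Reproduce the plan's total.** 4 × 54 = 216, as stated.

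**Step 2. Check the card statement in each cell.** The word 'or' can mean at least one drug (inclusive) or exactly one (exclusive).

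| Cell | Takes | Patients | True if 'or' is inclusive? | True if 'or' is exclusive? |
|---|---|---|---|---|
| A | neither | 54 | no | no |
| B | simvastatin | 54 | yes | yes |
| C | ondansetron | 54 | yes | yes |
| D | both | 54 | yes | no |

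- Inclusive: untrue for A only, 54/216 = 25%.
- Exclusive: untrue for A and D, (54 + 54)/216 = 108/216 = 50%.

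The 25% therefore holds on either reading. The 50% needs the exclusive one. Even where the inclusive reading makes the statement true for cell D, the card does not say that both drugs may be present.

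**Step 3. Ask whether the card reveals allocation.** If the text is identical for all 216 holders, the probability of belonging to any cell is the same after reading it as before: 54/216 = 25% for each cell, to anyone who knows the design. The card would carry information about allocation only if its text varied by arm. The article describes no such variation, and its Allocation section keeps the allocation from everyone on the team except the statistician and the pharmacist.

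**Step 4. Ask whether the analysis is affected.** The planned contrasts compare row means for ondansetron and column means for simvastatin. An identical card reaches both sides of each contrast, and the article gives no basis for a different effect in one cell. Sample size, power and significance level do not depend on the card.

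**The case against.** The strongest reply is that the sentence paraphrases the card and does not reproduce it. The full protocol and its appendices are not shown, and the printed card may be worded correctly. The article says several times that the trial is placebo-controlled and tests the drugs singly and together, so the loose 'or' could be condensation. This is a fair reason for a low grade. It does not remove the point, because this is the article's only account of the card's content and, taken as written, it contradicts Table 1. Wording carried over from the 36-patient feasibility study, which the article describes as adding ondansetron or simvastatin, is another possible explanation, but that is conjecture.

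A second reply concerns safety. The card names both study drugs, says that the holder is in a clinical study and lists trial contacts. A co-investigator or study doctor can be reached at any hour, and the treating consultant has agreed to the patient's participation. Patients also receive an information sheet and at least 24 hours to consider it. All of this stands, and it limits the practical harm. The card remains incomplete for a reader who has nothing else to hand.

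Three stronger readings are tempting, and the document does not support them.

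- *The card breaks the blind.* A reader might infer that it names each patient's own drug, that the copy in the notes then reaches the research assistants, who record drug treatment history and rate the PANSS, and that the primary outcome is compromised. That requires an arm-specific card. None is described, site staff are not given the allocation, and such a card would have no drug to name for the placebo-only cell.
- *The card inflates response in the comparator.* Any effect on expectation from an identical card would reach all four cells. No differential effect is shown.
- *The card is wrong for half the trial, without qualification.* That rests on the exclusive 'or'. Only 25% is certain.

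**Conclusion.** The point holds as an inconsistency in the description of a trial procedure. The card described under Randomization visit contradicts the double-blind placebo-controlled factorial design in the Overview and Table 1. Its statement is untrue for 54 of 216 patients (25%) on any reading and for 108 of 216 (50%) if 'or' is exclusive, and it tells nobody that both drugs or neither may be in use.

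This assumes that the sentence conveys the substance of the card, that the same card goes to all arms, that the planned 54 per cell is reached, and that the copies filed in the notes include the card. If the printed card already covers placebo and the combination, only the article's sentence needs correcting.

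Severity is minor. The consequence is inaccurate information for some participants and incomplete information for outside clinicians. No breach of the blind and no differential bias are shown, and no estimate, power figure or error rate changes.

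**What to change.** Reconcile the Randomization visit text with the Overview, Table 1 and Allocation. Use one card, identical for all arms, stating that the holder is taking part in a blinded placebo-controlled trial and may be receiving simvastatin, ondansetron, both or neither (placebo). Keep the trial contacts that are already listed. File the same generic wording in the medical notes, and say explicitly that neither the card nor the notes entry varies by arm, so that no site takes the sentence as a request to name a drug.

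The cost is rewording and reprinting one card, with replacement of cards already issued, since recruitment is under way. No extra patients, visits or staff are needed, and nothing in the analysis changes.
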